## Abstract

**Background:**

The main purpose of this study is to describe a protocol to compare the effectiveness of MIRP and conventional rehabilitation treatment.

**Methods/design:**

The study will be a single-blinded pragmatic randomized controlled trial involving patients (*N* = 100) with lung transplants. All patients will receive 6 weeks of treatment, while they will be divided into two groups and receive MIRP (*n* = 50) and conventional rehabilitation treatment (*n* = 50). Clinical functional assessment will be performed before, after intervention, and 3 months after the enrollment, respectively. Adults who have undergone unilateral or bilateral lung transplants and have just returned to the regular ward from the intensive care unit are eligible to participate.

**Discussion:**

The outcome of this study will provide a theoretical basis for clarifying intensive rehabilitation for lung transplants in future studies and clinical practice.

**Clinical trial registration:**

https://www.chictr.org.cn/showproj.html?proj=177086, identifier ChiCTR2200063538.

## Background

Lung transplantation (LT) is the ultimate treatment option for patients with end-stage lung disease (e.g., pulmonary fibrosis, bronchiectasis, and idiopathic pulmonary hypertension). Various complications and dysfunctions may occur after lung transplantation due to a variety of reasons, such as neuromuscular structural and functional abnormalities, the application of immunosuppressive drugs, and muscle wasting atrophy, which will bring about a series of problems, such as prolonged hospitalization, slow postoperative recovery, and increased therapeutic expenses (1). Previous studies have revealed that reduced exercise tolerance is common in postoperative lung transplant patients (2) and is associated with adverse health outcomes such as increased dyspnea and fatigue (3). Rehabilitation is a clinically proven effective physical factor to improve and reverse this quality-of-life decline (4, 5). Pulmonary rehabilitation (PR) is “a comprehensive intervention based on a thorough patient assessment followed by patient-tailored therapies that include, but are not limited to, exercise training, education, and behavior change, designed to improve the physical and psychological condition of patients and to promote the long-term adherence to health-enhancing behaviors” (6). The goal is to increase physiologic and functional status so that patients benefit from lung transplantation (7). New program models aimed at improving access and uptake have emerged in recent years, including tele-rehabilitation programs (8) and low-cost home programs (9), and the success of every rehabilitation program is evaluated in terms of whether the desired outcomes are achieved: these include improved exercise capacity, improved health-related quality of life, and reduced hospitalization rates (10).

Multimodal treatment is defined as applying several treatments simultaneously/concurrently or sequentially (one after another) to facilitate rehabilitation. The multiple modes used may include pharmacotherapy, devices, and behavioral/psychosocial interventions. The treatment was reported in treating different diseases: Parkinson’s disease (11), hemiplegic cerebral palsy (12), lung cancer surgery (13), spinal cord injury (14), etc. The structure and components of the multimodal exercise program were designed with reference to well-established protocols for patients with chronic obstructive pulmonary disease (COPD); one program included an 8-week (short-term) multimodal exercise program, containing inspiratory muscle training (IMT) plus neuromuscular electrical stimulation (NMES) (15); one program included 15 min of deep breathing exercises and 20–30 min of limb exercises (16); and one program combined health education, oral nutritional supplements, exercise, and oral testosterone for 90 days (17). The multimodal rehabilitation program (lasting 6 weeks) was developed in this study and encompasses postural support, respiratory exercises, exercise training with cycling and neuromuscular stimulation, daily living guidance for activities such as sitting balance and transfers, and early swallowing assessment and training to enhance oral feeding capabilities. Intensive rehabilitation aims to help patients regain function as soon as possible, improve quality of life, and increase survival and long-term quality of life through systematic rehabilitation interventions and treatments. Intensive rehabilitation was developed in this study, which was implemented 5–6 days per week and consisted of chest physical therapy techniques, inspiratory muscle strength training, and increasing exercise training, all under the supervision of a physiotherapist.

For this clinical study, we would assess 6 min walk distance (6MWD) as the primary clinical outcome. Previous studies have established an association between 6MWD and survival in patients after solid organ transplantation; shorter 6MWD is associated with increased risk of death, hospitalizations, and worse quality of life in patients evaluated for liver transplantation (18). There have been two key randomized clinical trials (RCTs) evaluating the impact of pulmonary rehabilitation (PR) on standard care after LT (19, 20). However, it remains difficult to conclusively attribute improvements in exercise capacity to the intervention itself. This is primarily due to the significant confounding factor of natural postoperative recovery. Furthermore, the minimal clinically important difference (MCID) for the 6MWT in an LT population has not been established, making it challenging to interpret the true clinical significance of any observed changes. This study aimed to contribute to this evidence base by evaluating a novel multimodal rehabilitation protocol.

Potential limitations of all previous RCTs that examined post-LT interventions include: (1) none used multimodal interventions, (2) the majority of studies were at high risk of bias, (3) lack of follow-up, and (4) some studies did not report critical outcomes such as 6 min walk distance. Thus, high-quality RCTs are needed. While previous studies with single interventions have demonstrated some effectiveness (10, 21), multimodal approaches have not been examined in individuals undergoing lung transplant (LTx). However, multimodal and multidisciplinary aftercare intervention was recommended after kidney transplantation (KTx); the intervention significantly improved outcomes after KTx (22). This study is a randomized controlled trial (RCT) designed to evaluate a novel MIRP against usual care in LTx recipients. Recognizing that conventional post-transplant rehabilitation often lacks the intensity and multidisciplinary focus needed to address multifaceted recovery challenges, MIRP integrates structured, high-frequency components—including chest physiotherapy, progressive strength training, and swallowing therapy—to target these evidence gaps directly. This report describes the research design and protocol for implementing and assessing this RCT.

### Study hypothesis and objective

This protocol was written in accordance with the Standard Protocol Items: Recommendations for Interventional Trials (SPIRIT) (23). Participants were recruited from the Lung Transplantation Department of the Center of Respiratory Diseases, China-Japan Friendship Hospital, China. The multimodal intensive rehabilitation program is designed to comprehensively improve patients’ respiratory muscle function, voice and swallowing function (24), and limb strength, thereby shortening hospital stay and improving the quality of life. The primary outcome was to analyze the effects of MIRP on the 6 min walking distance in lung transplant recipients. Secondary outcomes were (1) short-term change in health-related quality of life; (2) body skeletal muscle mass and skeletal bone condition; (3) respiratory muscle function and lung function; (4) psycho-emotional states; (5) the state of swallowing function and nutrition; (6) Clinical Frailty Scale; and (7) adverse events related to rehabilitation.

## Method/design

### Study design

The inclusion criteria are as follows: (1) recipients of unilateral or bilateral lung transplantation and (2) age between 18 and 75 years.

The exclusion criteria are as follows: (1) inability to obtain informed consent from the patient or a legal representative; (2) severe postoperative complications, such as anastomotic leakage, pulmonary embolism, or other major complications requiring prolonged mechanical ventilation or reoperation; (3) dependence on invasive mechanical ventilation or endotracheal intubation when transferred back to the general ward; (4) hemodynamic instability, defined as mean arterial pressure (MAP) < 60 mmHg or > 110 mmHg, heart rate < 50 bpm or > 130 bpm, or the requirement for high-dose vasoactive agents (e.g., norepinephrine > 0.1 μg/kg/min); (5) insufficient respiratory reserve, defined as a ratio of arterial oxygen partial pressure to inspired oxygen fraction (P/F ratio) ≤ 300, or oxygen saturation (SpO₂) ≤ 90% while receiving an inspired oxygen fraction (FiO₂) ≥ 0.6; (6) unstable cardiovascular conditions, including recent myocardial infarction, uncontrolled hypertension, unstable angina, severe arrhythmias, or advanced heart failure; (7) neurological or psychiatric disorders that interfere with rehabilitation participation, such as uncontrolled seizures, severe cognitive impairment, or severe psychiatric illness; and (8) musculoskeletal limitations that preclude active participation in rehabilitation, such as severe arthritis, recent fractures, or recent orthopedic surgery. The withdrawal criteria are as follows: (1) patient or legal representative requests to withdraw consent; (2) development of severe medical complications after enrollment that preclude safe participation in the rehabilitation program; (3) clinical deterioration requiring transfer to the ICU or re-initiation of invasive mechanical ventilation; (4) any adverse events deemed by the treating physician to require discontinuation of the intervention for patient safety; and (5) non-compliance with study procedures that prevents adequate data collection.

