### Sample size

The significance level is set at 0.05, corresponding to a Z-value of 1.96. The power of the test is 90%, corresponding to a Z-value of 1.28. The assumed mean 6MWD values (339 m for the MIRP group and 320 m for the control group) and standard deviations for both variables are given as 20 m, and the resulting effect size used for the sample size calculation was derived from our center’s preliminary pre-study data. These estimates were based on an initial analysis of a small cohort of patients who underwent the intervention protocol prior to the initiation of this formal randomized controlled trial. Finally, there is a non-inferiority margin, denoted as *Δ* = 30, which requires 35 patients per group. A 5% dropout rate has also been accounted for, resulting in the target of 50 participants per group (100 in total).

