### Outcome measurement

The selection of assessment time points was based on clinical relevance and the study objectives. The 6-week assessment was chosen to evaluate the short-term efficacy and immediate impact of MIRP upon completion of the supervised, intensive intervention phase. The 3-month assessment serves as a key mid-term follow-up point to determine the sustainability of initial gains and to capture clinically significant outcomes as patients transition into the maintenance phase of recovery. All outcome assessments will be conducted by trained research assistants who are blinded to the participants’ group allocation. The primary outcome measure of treatment failure is assessed at 3 months after recruitment. The following are assessed at 6 weeks and 3 months after recruitment, including:

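### The withdrawal criteria merge stopping the programme with leaving the study, and nothing says that 6-week and 3-month outcomes are still collected, so 6MWD may be lost informatively

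*Protocol article*

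**What the plan says.** The Study design section gives five withdrawal criteria. The first is a request by the patient or representative to withdraw consent. The others are events after enrolment.

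Criterion (4) ties withdrawal to the end of treatment: "any adverse events deemed by the treating physician to require discontinuation of the intervention for patient safety". Two further criteria concern patients whose course worsens. One of them, criterion (3), reads "clinical deterioration requiring transfer to the ICU or re-initiation of invasive mechanical ventilation". The other, criterion (2), is broader and covers "development of severe medical complications after enrollment that preclude safe participation in the rehabilitation program". The last, criterion (5), is about obtaining data and not about tolerance of the programme: "non-compliance with study procedures that prevents adequate data collection".

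The section does not say what withdrawal means for later assessments.

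The objectives section names 6MWD as primary: "The primary outcome was to analyze the effects of MIRP on the 6 min walking distance in lung transplant recipients". The Outcome measurement section sets assessments at 6 weeks and 3 months, but words the primary outcome differently: "The primary outcome measure of treatment failure is assessed at 3 months after recruitment". The Blinding section states that participants and care providers know the allocation.

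**The concern.** Stopping a treatment and leaving a trial are different events. A patient who can no longer follow the programme can usually still be assessed, and a comparison of randomised groups needs that assessment. Here both events fall under one label. Criterion (4) goes furthest, because it makes discontinuing the intervention itself a ground for withdrawal.

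The patients affected are not a random subset. Criteria (2) and (3) pick out those who are deteriorating. Criterion (4) rests on the judgement of a treating physician who knows the allocation. If site staff take withdrawal to end assessment, poor walkers go missing because they did badly. If this happens more often in one arm, the remaining groups are no longer comparable.

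A statistical analysis plan can choose the analysis set and the missing-data method. It cannot supply walk tests that were never done. Whether outcomes are collected is a matter of trial conduct, and the withdrawal rule is where that is settled.

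**Working it through.** **Step 1. Is continued follow-up stated anywhere else?**

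| Section | What it says | Does it settle the question? |
|---|---|---|
| Common rehabilitation methods (text after Figure 2) | An unsupervised plan runs to the 3-month assessment, in or out of hospital | No. It deals with discharge, not withdrawal |
| Recruitment | Patients who become eligible only after 3 days are left out of the analysis | No. They are never enrolled |
| Sample size | 5% dropout is allowed for | No. Dropout is neither defined nor split by arm |
| Trial status | Refers to following up all enrolled patients | No. It is a remark on safety and status, not a rule |

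**Step 2. Could withdrawal differ by arm?** The two arm descriptions differ in load: seated cycling five against three times a week, resistance training twice against once, swallowing therapy three times against twice, and electrical stimulation in the MIRP arm only. MIRP therefore gives more occasions for a session-related event. Better recovery under MIRP could equally make deterioration rarer there. The sign is open.

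**Step 3. General formula.** Let w be the proportion withdrawn in an arm and D the amount by which the withdrawn walk less than the completers. The completer mean exceeds the all-patient mean by w × D. With the same D in both arms, the bias in the arm difference is (w1 − w0) × D. It is zero if w1 = w0. With equal w it arises only if D differs by arm.

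**Step 4. Illustration at the planned SD.** From the Sample size section: means 339 and 320 m (difference 19 m), SD 20 m, critical value 1.96 ("The significance level is set at 0.05, corresponding to a Z-value of 1.96"), 50 per arm. Assumed, because the article gives neither: the withdrawal proportions, and a correlation ρ of 0.3 to 1.0 between frailty and 6MWD. The frailest fraction w is removed from a normal distribution, so the completer mean rises by ρ × 20 × φ(z_w)/(1 − w).

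For 15% on MIRP and 5% on control with ρ = 1:

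- MIRP: 20 × 0.2332/0.85 = 5.49 m
- Control: 20 × 0.1031/0.95 = 2.17 m
- Difference: 3.3 m; with ρ = 0.3 it is 1.0 m
- SE = 20 × √(1/42.5 + 1/47.5) = 4.22 m

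| Withdrawn, MIRP vs control | Bias if the true effect is 0 | Two-sided type I error (nominal 5%) |
|---|---|---|
| 5% vs 5%, or 30% vs 30% | 0 m | 5.0% |
| 10% vs 5% | 0.5 to 1.7 m | 5.2 to 7.0% |
| 15% vs 5% | 1.0 to 3.3 m | 5.6 to 12.3% |
| 30% vs 10% | 1.8 to 6.0 m | 6.9 to 26.8% |

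**Step 5. Patients who cannot walk.** Step 4 draws the withdrawn from the tail of an SD-20 distribution, so it cannot represent them. If they were scored 0 m against the control mean of 320 m, a 5-point difference in withdrawal would give 0.05 × 320 = 16 m, or 16/19 = 84% of the planned difference. Both the 5 points and the score of 0 m are assumptions.

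**Step 6. Precision.** The stated target is 90% power ("The power of the test is 90%, corresponding to a Z-value of 1.28"). On the planned values, power for 19 m is Φ(19/(20√(2/n)) − 1.96): 97.8% at n = 35 and 99.7% at n = 50 per arm. Loss of patients therefore threatens validity more than power. How the article arrives at 35 and 50 is a separate question and is not relied on here.

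**The case against.** The strongest defence is that the article never says what withdrawal entails. Criteria (2) and (4) are worded around taking part in the programme, so withdrawal from the intervention alone is a fair reading. An article may also leave analysis sets and missing data to a fuller document. This stands to the extent that the text is open to two readings. It does not remove the point: the same list contains withdrawn consent, which does end participation, and no sentence keeps the other patients under assessment.

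A reader might infer more than the documents support, in three ways.

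- **That 6MWD is compared only among patients who tolerate the programme.** No section declares a completer or per-protocol analysis. The article states no analysis set at all.
- **That poor adherence leads to removal.** Criterion (5) covers only non-compliance that prevents data collection. It describes data that cannot be obtained, and deleting it would recover no walk test.
- **That the false-positive rate is badly inflated.** With 45 per arm and SD 20 m, SE = 20 × √(2/45) = 4.22 m. A 10-point difference in withdrawal and a 100 m deficit give a 10 m bias and about 66% type I error; the 16 m of Step 5 gives 97%. The arithmetic is right, but the deficits are 5 and 16 SDs. Even perfect removal of the lowest 10% leaves the withdrawn only about 1.95 SD = 39 m below the rest. Such figures need a separate group of withdrawn patients, and the documents give neither its size nor its walking distance. At an assumed SD of 60 m, the 10 m bias gives about 12%.

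It can also be said that, if treatment failure is the primary outcome, a deterioration might be an outcome event and not a loss. The article does not define treatment failure, so this cannot be settled. That reading would make continued ascertainment more important.

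**Conclusion.** The point holds as a risk created by the wording of the withdrawal rule, not as a demonstrated bias. Criteria (2) to (4) join stopping the programme to leaving the study, and the article does not say that outcomes are still collected afterwards. Followed literally, the rule can remove the patients who fare worst, on decisions partly made by unblinded clinicians, in a trial whose arms differ in intensity.

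The size and sign of any bias cannot be fixed from the document. Bias arises mainly if withdrawal differs by arm. At the planned SD of 20 m and an assumed 15% against 5% withdrawn, it is about 1 to 3 m (5 to 17% of the planned 19 m); with equal withdrawal the illustration gives none. It would be larger if the withdrawn include patients who cannot walk. The correction is worth making before database lock, because no later analysis can replace assessments that were not done.

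**What to change.** Change the Study design section as follows, leaving the clinical stopping rules themselves unchanged:

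1. Relabel criteria (2) to (4) as reasons to discontinue the rehabilitation programme only.
2. State that only withdrawal of consent to follow-up ends outcome collection.
3. Treat criterion (5) as missing data, recorded with its reason, and not as grounds for removal from the analysis.
4. State that all randomised patients are assessed at 6 weeks and 3 months where possible and analysed in the arm to which they were randomised.
5. Prespecify in the statistical analysis plan how death and inability to walk are handled. Scoring 0 m or a worst rank is one option among several, and the choice should be justified there.

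The cost is protocol wording, a few extra walk tests or status checks, and possibly a larger variance of 6MWD. The Trial status section reports recruitment ongoing in August 2025 and lock planned for December 2025, so assessments already missed cannot be recovered. For patients already withdrawn, the reason, the date and the arm should be reported.

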### Participant timeline

This study is ongoing and started in September 2024, ending in December 2025. The schedule for enrollment, interventions, and assessments is presented in Figure 1.

**Figure 1 fig1:**
[figure not shown]
Study schematic diagram. MRCs, Medical Research Council sum score; MVC, maximum voluntary contraction (specifically for knee extension strength); PFITs, physical function in intensive care test—scored; MIP, maximum inspiratory pressure; PIF, peak inspiratory flow; PCF, peak cough flow; PEF, peak expiratory flow; EAT-10, 10-item Eating Assessment Tool; TOR-BSST, Toronto Bedside Swallowing Screening Test; MASA, Manchester Orofacial Assessment (likely a specific version); body composition assessment; BIA, bioelectrical impedance analysis; activities of daily living (ADL) assessment; BI, Barthel Index; MIRP: (Context suggests a specific rehabilitation protocol, e.g., multimodal intensive rehabilitation program. The exact term was not spelled out in the image). NMES, neuromuscular electrical stimulation; Quadriceps NMES, neuromuscular electrical stimulation for the quadriceps muscle; breath muscles NMES, neuromuscular electrical stimulation for the respiratory muscles; IMT, inspiratory muscle training; ACTs, active cycle of breathing techniques; OPEP, oscillating positive expiratory pressure; ACBT, active cycle of breathing technique; 6MWT, 6-min walk test (measures exercise capacity); QoL, quality of life; SF-36, 36-Item Short Form Health Survey; SGRQ, St. George’s Respiratory Questionnaire.

### Sample size

The significance level is set at 0.05, corresponding to a Z-value of 1.96. The power of the test is 90%, corresponding to a Z-value of 1.28. The assumed mean 6MWD values (339 m for the MIRP group and 320 m for the control group) and standard deviations for both variables are given as 20 m, and the resulting effect size used for the sample size calculation was derived from our center’s preliminary pre-study data. These estimates were based on an initial analysis of a small cohort of patients who underwent the intervention protocol prior to the initiation of this formal randomized controlled trial. Finally, there is a non-inferiority margin, denoted as *Δ* = 30, which requires 35 patients per group. A 5% dropout rate has also been accounted for, resulting in the target of 50 participants per group (100 in total).

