## Discussion

Researchers have described MIRP, an intensive pulmonary rehabilitation (PR) program tailored for pediatric patients after lung transplantation. A case report (25) suggested its potential feasibility and indicated possible improvements in functional exercise capacity, lung function, and quality of life in a 10-year-old recipient. However, as this was a single-case study with inherent limitations such as selection bias and lack of generalizability, further evidence from larger cohort studies or controlled trials is needed to conclusively establish the efficacy and safety of implementing such intensive PR programs in the broader pediatric lung transplant population. Moreover, the mechanisms underlying improvement in exercise capacity with MIRP among patients after LT are not well understood. With regard to the influential factors, peripheral muscle abnormalities have been shown to be the predominant limiting factor to exercise capacity in LT recipients; in addition, the original lung disease and pathophysiology may also influence an individual’s exercise capacity and physical activity (26). Recent studies have shown that exercise contributes to significant improvements in central pulmonary perfusion and peripheral skeletal muscle function that are beneficial for improvement in exercise capacity. This is probably because improved pulmonary perfusion is likely to lead to improved oxygenation and cardiac output and, thus, improvement in exercise tolerance and cardiorespiratory fitness (9). Moreover, Memme et al. (27) reported that exercise could help adjust the volume, structure, and capacity of mitochondria; thus, MIPR may help alleviate the muscle atrophy and damage to the respiratory function of mitochondria resulting from long-term immobilization before and after LT and the use of immunosuppressive drugs.

This study will provide new foundational data to determine whether an integrated model combining chest physical therapy, rehabilitation exercise training, nutrition, and swallowing management can improve physical endurance and quality of life after lung transplantation (24, 28). As intended by Chinese medical organizations, this study has the potential to optimize lung transplantation care in China, and all elements that are positively evaluated in our study have the potential to become part of standard medical care in China. If successful, our plan will expand to other transplanted organs and all regions of China.

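### The sample size rests on an unexplained 30 m non-inferiority margin although the trial asks whether MIRP improves outcomes, and the 35 and 50 per group do not follow from the stated inputs

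*Protocol article*

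**What the plan says.** The Sample size section of the protocol article gives these inputs:

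- Alpha: "The significance level is set at 0.05, corresponding to a Z-value of 1.96".
- Power: "The power of the test is 90%, corresponding to a Z-value of 1.28".
- Expected mean 6MWD: "339 m for the MIRP group and 320 m for the control group", a 19 m advantage for MIRP.
- Spread: "standard deviations for both variables are given as 20 m".
- Margin: "Finally, there is a non-inferiority margin" of 30 (no unit given; metres are implied).

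It says that the margin leads to 35 per group and that a 5% dropout allowance brings this to 50 per group, 100 in total. The means and SD come from a small pre-study cohort at the centre.

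Elsewhere the language is about improvement. The Discussion asks whether the integrated model "can improve physical endurance and quality of life after lung transplantation". The study hypothesis section describes the programme as built to improve respiratory, swallowing and limb function. The Background says that conventional rehabilitation often lacks the needed intensity, and presents the trial as "designed to evaluate a novel MIRP against usual care in LTx recipients". It also says that a minimal clinically important difference for the walk test "in an LT population has not been established".

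**The concern.** MIRP is the heavier arm. Compared with control it adds phrenic, neuromuscular and pharyngeal stimulation, more frequent seated cycling, resistance training and swallowing therapy, and a nutrition specialist. For such a programme the useful question is whether patients do better. Showing that they do not do much worse would matter only if MIRP offered some offsetting advantage, and the article claims none.

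The sample size is nevertheless tied to a non-inferiority margin. If that framing reached the analysis, a programme with no effect, or one moderately worse than usual care, could be reported as a success. The margin also enters the arithmetic behind the stated group size, so it cannot be passed over as a stray word: removing it removes the only derivation that the article offers.

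**Working it through.** **Inputs.** All are from the Sample size section: z-values 1.96 and 1.28 (sum 3.24), difference 339 − 320 = 19 m, SD 20 m, margin 30 m, dropout 5%.

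**1. Can 35 per group be reproduced?** The usual formula for two means is n per group = 2 × (SD × 3.24 / distance)², where distance is how far the expected difference lies from the null boundary.

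| Case | Distance | Result | n per group |
|---|---|---|---|
| Non-inferiority, 19 m benefit credited | 30 + 19 = 49 | 3.50 | 4 |
| Non-inferiority, no true difference | 30 | 9.33 | 10 |
| Non-inferiority, 19 m taken off the margin | 30 − 19 = 11 | 69.4 | 70 |
| Superiority | 19 | 23.3 | 24 |

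With one-sided alpha 0.05 instead, the three non-inferiority cases become 4 → 3, 10 → 8 and 70 → 57, and superiority becomes 19. None gives 35. The figure appears only as (20 × 3.24 / 11)² = 34.7, rounded up. That expression takes the expected benefit off the margin, although a benefit moves the trial away from a non-inferiority boundary, and it omits the factor 2 for two groups.

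**2. Does 35 become 50?** 35 / 0.95 = 36.8, so 37 per group. Going from 35 to 50 would need a dropout of 1 − 35/50 = 30%.

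**3. What would the margin allow?** Suppose success were claimed on it. With 50 per group and 5% dropout, 50 × 0.95 = 47.5, so take 47 evaluable. The standard error is 20 × √(2/47) = 4.13 m. Non-inferiority is declared when the observed difference exceeds −30 + 1.96 × 4.13 = −21.9 m. The probability of that is Φ((30 + true difference)/4.13 − 1.96):

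| True difference, MIRP − control | Probability of claiming non-inferiority |
|---|---|
| 0 m | >99.99% |
| −10 m | 99.8% |
| −15 m | 95% |
| −20 m | 68% |

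**4. What does a superiority trial need?** For 19 m, SD 20 m, two-sided 0.05 and 90% power, the normal formula gives 24 per group and the t distribution gives 25 (power 89.6% at 24, 90.8% at 25). After 5% dropout, 24 / 0.95 = 25.3, so 26 per group; starting from 25 it is 27.

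**5. What do the planned 100 patients give for superiority?** The SD of 30 or 40 m is an assumption, included because the 20 m comes from a small cohort.

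| SD | n per group for 90% power | Power at 50 per group | Power at 47 per group |
|---|---|---|---|
| 20 m | 24 | 99.7% | 99.6% |
| 30 m | 53 | 89% | 87% |
| 40 m | 94 | 66% | 63% |

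**The case against.** The strongest reply is that the article states no primary test and no success rule. Non-inferiority occurs once, as a sample size input, and an analysis plan that is not shown may specify superiority. This is right as far as it goes. A reader might infer that the trial is committed to a non-inferiority conclusion, or cannot answer its own question. The document supports neither. A superiority comparison can be read from the same confidence interval, and on the stated inputs it is well powered. The probabilities in step 3 are therefore conditional on success being claimed on the margin. An unseen plan would not, however, remove the contradiction within the protocol article or supply a derivation for 35.

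Three other inferences are tempting and should not be drawn:

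- **That the fault is a margin larger than the 19 m gain.** The margin lies below zero and the expected gain above it. A non-inferiority result would fail to show improvement with a 5 m margin too; the width only makes matters worse.
- **That 30 m is a gain MIRP must exceed.** The text calls it a non-inferiority margin outright.
- **That MIRP is the costlier arm.** The article gives no costs.

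It is also fair to say that the improvement aim is drawn from the programme description and the Discussion. The Background phrase about evaluating MIRP against usual care, and the primary objective of analysing effects on 6MWD, are neutral between the two kinds of hypothesis. Nor does the lack of an established important difference by itself prove a margin baseless. What stands is that the article offers no justification for 30.

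**Conclusion.** The point holds as a contradiction between the basis of the sample size and the question of the trial, together with a derivation that does not work. It is not a finding of low power. The group size of 35 comes from no standard formula on the stated inputs, and 50 does not follow from 35 with 5% dropout. A non-inferiority claim at 30 m would be almost certain at no effect and 95% likely with MIRP truly 15 m worse, given SD 20 m, 47 evaluable per arm and a 1.96 critical value. On the same SD the 100 patients are ample for superiority at 19 m. That reassurance depends on the SD: power falls to about 89% at 30 m and 66% at 40 m with 50 per group. It should be corrected before the data are analysed, because an unexplained wide margin left in the protocol could be used after a null result.

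**What to change.** By dated amendment before database lock, which the Trial status section plans for December 2025:

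1. Delete the non-inferiority margin from the Sample size section.
2. State a two-sided superiority hypothesis for 6MWD at alpha 0.05, with success only if the 95% confidence interval for MIRP minus control lies wholly above 0.
3. Name one time point for it, and reconcile this with the Outcome measurement section, which calls the primary outcome treatment failure at 3 months.
4. State that non-inferiority will not be claimed.
5. Replace the derivation of 35 and 50 with the superiority calculation: about 24 to 25 per group, about 26 after 5% dropout, for 19 m, SD 20 m and 90% power.
6. Keep the 100 patients as a stated choice and report the power that they give across SDs of 20, 30 and 40 m.

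The cost is an amendment with its approvals, and matching wording in the analysis plan. No added patients are needed on the stated assumptions. If the SD is nearer 30 or 40 m, 50 per group falls short of 90% power, and the text should say so.
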